### Inclusion criteria

1) Sick leave due to LBP for 2-10 months

2) At least 50% sickness compensation

3) Both participant and clinician agree that randomization is acceptable

4) Written informed consent from the participant

5) At least 50% employed

6) One of the following ICPC diagnoses: L02, L03, L84, or L86

7) Age between 20 and 60 years

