
#### 2. BI and CBT

Seven sessions of individual CBT, over a period of 2-3 months, will be given in addition to the BI. The CBT builds on the message contained in the BI, and is theoretically based on [name]'s CBT model for CFS patients [17], and on the Cognitive Activation Theory of Stress (CATS) [5]. This CBT model assumes that cognitive, emotional, physiological, and behavioral responses are linked, and that changes in one of these areas will result in changes in others. During the treatment, patients are helped to change their interpretation of the pain and associated fear, symptom focusing, and avoidance. Participants are encouraged to see complaints as temporary and reversible, and not as signs of harm, or as evidence of a permanent condition or as a fixed disease pathology. The aim of the intervention is to help patients change cognitive- and behavioral factors assumed to be partly responsible for the maintenance of symptoms and disability. Return to work is an outlined goal of the treatment.

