### Analysis strategy

#### Primary analyses of efficacy

Sick leave/insurance status will be calculated as risks of shifting between different states of sick leave, disability pension, and recovered. The outcome from the participating clinics will be combined if no gross center effect is found. The analyses will follow the "intention to treat" principle. Per protocol analysis will also be performed. The proportions of participants with a positive primary outcome will also be compared across the treatment groups. If there are significant differences, we will estimate the number of participants that need to be treated in order for one additional participant to benefit (NNT), compared to the least effective therapy. A Cox-proportional hazards model may model the transitions between the different states. Regression models for the transition probabilities will also be performed. Explanatory variables (treatment) and confounders (e.g. age, gender) will be included as in any regression model. Possible changes in diagnosis and other characteristics will be built in. Partial recovery represented by partial sick leave will be accounted for.

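### The sentence that builds changes in diagnosis and other characteristics into the primary regression models permits adjustment for post-randomisation variables, contrary to the stated intention-to-treat principle

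*Protocol article*

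**What the plan says.** All of the analysis text is in the protocol article under Primary analyses of efficacy. The outcome is the risk of moving between sick leave, disability pension and recovery. A Cox model is optional; in addition, "Regression models for the transition probabilities will also be performed". The covariates follow: "Explanatory variables (treatment) and confounders (e.g. age, gender) will be included as in any regression model". The next sentence is "Possible changes in diagnosis and other characteristics will be built in", and the one after it is "Partial recovery represented by partial sick leave will be accounted for".

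The same section also says "The analyses will follow the 'intention to treat' principle" and plans an analysis for which no covariates are mentioned: "The proportions of participants with a positive primary outcome will also be compared across the treatment groups".

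Two other places bear on the point. Inclusion criteria requires "One of the following ICPC diagnoses: L02, L03, L84, or L86", so diagnosis is settled before allocation. The section on BI and CBT says the therapy is meant to "help patients change cognitive- and behavioral factors assumed to be partly responsible for the maintenance of symptoms and disability".

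**The concern.** Age and gender cannot be altered by treatment. A change in diagnosis during follow-up can be, and the other characteristics are not named, so nothing keeps the treatment's own targets out of the list.

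Conditioning on a variable that allocation has influenced does two things. If the change itself affects return to work, the part of the treatment effect that runs through it is taken out of the coefficient. If the change and return to work share an unmeasured cause, conditioning on the change also creates an association between arm and that cause, even where treatment does nothing to the outcome.

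At stake is what the treatment coefficient in the primary regression models means. It would not be the effect of assignment. An open list of post-baseline adjusters on the primary outcome also leaves room for choosing the model after seeing the data.

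**Working it through.** **1. The plan's own figure.** Inputs from Sample size calculations: 40% versus 60%, power 80%, significance level 5% (taken as two-sided), equal arms.

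n = [1.96·√(2·0.5·0.5) + 0.842·√(0.4·0.6 + 0.6·0.4)]² / 0.20² = (1.386 + 0.583)² / 0.04 = 96.9, so 97 per arm and 4 × 97 = 388.

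This agrees with the plan. The point does not rest on a wrong number.

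**2. Reading the sentence.** Three facts favour the covariate reading. The sentence directly follows the covariate sentence. The section has already listed its outcome states, and diagnosis is not one of them. The unnamed other characteristics are hard to read as states. The timing follows from diagnosis being an entry criterion.

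**3. Route one: the change lies between treatment and outcome.** Let m be the shift in frequency of the change caused by treatment, and e the effect of the change on return to work. On the additive scale, with a total effect of 0.20, the adjusted difference is 0.20 − m·e. Neither m nor e is in the document; both are assumed. Power is for 97 per arm with control at 40%.

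| m | e | Adjusted difference | Power |
|---|---|---|---|
| 0 | 0.2 or 0.4 | 0.20 | 80% |
| 0.1 | 0.2 | 0.18 | 71% |
| 0.1 | 0.4 | 0.16 | 61% |
| 0.2 | 0.2 | 0.16 | 61% |
| 0.2 | 0.4 | 0.12 | 39% |
| 0.3 | 0.2 | 0.14 | 50% |
| 0.3 | 0.4 | 0.08 | 20% |

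The sign is not fixed either. If m·e is negative, for example −0.1 × 0.4, the adjusted difference is 0.20 + 0.04 = 0.24, an overstatement.

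**4. Route two: shared unmeasured cause, no treatment effect on the outcome.** Assume a binary cause U with prevalence 0.5, P(change) = 0.2 + a·T + b·U, and P(return to work) = 0.3 + b·U. The true treatment effect is zero. The linear-model coefficient for T after adjusting for the change is −a·(b²/4)/V, where V is the mean within-arm variance of the change.

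- a = 0.2, b = 0.2: −0.2 × 0.01/0.23 = −0.009
- a = 0.2, b = 0.4: −0.2 × 0.04/0.24 = −0.033
- a = 0.3, b = 0.4: −0.3 × 0.04/0.225 = −0.053

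A simulation of 400,000 patients gave −0.007, −0.035 and −0.055, against unadjusted differences of about 0. The formula carries the factor a, so in this model the bias vanishes when allocation does not affect the change.

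**5. Both routes together.** Assume a direct effect of 10 points, a 30-point penalty for a change, a change in 33% of controls, and a standard normal unmeasured cause. If treatment lowers the change rate to 24%, 17% or 12%, the total effects are 12.3, 14.6 and 16.2 points and the adjusted ones 8.9, 8.3 and 7.7, a loss of 28% to 52%. If changes occur in only about 4% of controls, the loss is about 6% to 9%. If treatment does not affect the change, both estimates are about 9.8 points and nothing is lost.

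**The case against.** The strongest reply is that the plan never says these changes enter as covariates. The covariate sentence has its own verb and names only baseline variables. The sentence that follows the disputed one concerns partial sick leave, which is a matter of outcome states. A sick-leave spell recorded under a new diagnosis could be handled as a state or transition, and then nothing need be adjusted away. A further reading is that the change meant is one found at the clinic examination: BI includes diagnostic clarification and is given before randomisation, so a diagnosis revised there would be a legitimate baseline value. Both readings are possible. Neither is stated, and the text as written still allows the harmful one.

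A second reply is that no section expects CBT to alter a coded ICPC diagnosis; its targets are interpretation, fear and avoidance. That is correct for diagnosis. It does not cover the unnamed other characteristics.

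A third is that the comparison of proportions remains. This stands. A reader might infer that the randomised comparison is lost for the whole trial. The document does not support that: the comparison of proportions mentions no covariates, and it matches the contrast used for the sample size. However, it is listed as an additional analysis with no stated precedence over the regression models.

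A fourth is that an article leaves covariate timing to the analysis plan. Silence would be no finding. Here the article states a rule, and an analysis plan that follows it would inherit the problem.

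**Conclusion.** The point holds for the primary regression models. On its most natural reading, the sentence adjusts them for post-randomisation variables. That can bias the treatment coefficient where allocation affects those variables, whether because they lie on the path to return to work or because they share unmeasured causes with it. It also conflicts with the intention-to-treat principle in the same section.

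Size and direction cannot be derived from the document. Over the assumed range in the table, a 20-point difference becomes 20 to 8 points and power 80% to 20%. A reader might infer that a CBT benefit will be understated by a known fraction, such as 28% to 52%. That fraction rests wholly on assumed change rates and effects, and it is zero in the same model when treatment does not affect the change. The sample size of 97 per arm is not in question.

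**What to change.** State that covariates in the Cox and transition models used for the primary analysis are limited to values fixed before randomisation: the stratification factors clinic and gender, plus age and baseline ICPC diagnosis (the last one recorded before allocation).

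Replace the disputed sentence rather than only deleting it, since deletion could remove a legitimate handling of outcome states. The new text should say one of two things: that a change in diagnosis, or in any other named characteristic, is a defined state or transition in the multi-state outcome; or that such changes are analysed only in a separate model labelled exploratory, for example a mediation analysis.

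The cost is wording only. Randomization says that the research unit receives gender, age and diagnoses before disclosing the allocation, and clinic is a stratification factor. No data are added, and the 97 per arm and its 80% power for 40% versus 60% are unchanged. The change should be made before the allocation code is opened.

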### Number and source of participants

The goal is to recruit 400 participants (age between 20 and 60 years) to the trial (see sample size calculations). The Norwegian National Insurance Administration (NAV) will send a letter of invitation to patients that have been at least 50% sick listed, for 2 to 10 months due to LBP. In Norway, at any point in time, there are approximately 14000 patients on sick leave for 6 months, due to low back pain ([name], NAV, personal communication). Patients on sick leave that geographically belong to one of the participating clinics are invited to participate in the study. The letters of invitation will be sent from NAV, and will include information about the study, and a response sheet. If a patient is interested in participating in the study, he or she fills out their contact information on the response sheet, and returns it to the research unit (Uni Health). After the response sheet has been received, the patients will be invited to the participating local back pain/pain clinic for a final evaluation for inclusion into the study. For those included, baseline assessment, BI, and randomization to any of the four interventions will be performed.

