### Exclusion criteria

1) Less than 50% sick listed or not on sick leave anymore

2) Pregnancy

3) Hemophilia

4) Osteoporosis (known osteoporotic fracture, or on anti osteoporostic medication)

5) Currently being treated for cancer

6) Recent back trauma

7) Serious psychiatric disorders (mainly due to ongoing psychosis, high suicide risk, and/or serious depression), assumed to be incompatible with participation in the trial.

8) Not fluent in Norwegian (assumed to be incompatible with CBT)

9) Debilitating Cardiovascular disease

10) Patients on warfarin treatment (blood thinner, e.g. Marevan)

11) Ongoing insurance trial, lawsuit, or pending legal action for LBP or related conditions

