### Randomization

The patients will be randomized, using concealed randomization, to one of the following four treatments; 1) BI only, 2) BI and CBT, 3) BI and seal oil, or 4) BI and soy oil. This is done according to a computer generated randomization list, generated by the trial statistician. The list is stratified by clinic and gender. A central telephone randomization system, as already set up by our research unit will be used. At each of the participating clinics, a research assistant that is not involved in the treatment calls the research unit (Uni Health) to get information on which treatment the patient is randomized to. The research unit receives information about the patient's id number, gender, age, and diagnoses before the treatment allocation is disclosed, ensuring that the sequence is concealed until the intervention is assigned. The allocation code, including details of block size etc. will not be revealed to the researchers or the clinicians until recruitment, data collection, and laboratory analyses are complete. For those patients allocated to nutritional supplementation, the clinics provide blinded boxes, containing capsules with either seal oil or soy oil. All researchers, clinicians, and participants are blinded to treatment allocation of individual participants for the nutritional supplementation. Researchers at Uni Health, the trial statistician, and those assessing the main outcome of the study will be blinded to group assignment. Patients and CBT clinicians will not be blinded to group assignment.

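### Partial sick leave is used as the marker of partial recovery without reference to the level at entry, yet patients can be randomised while already on partial sick leave

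*Protocol article*

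**What the plan says.** All references are to the protocol article.

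- **Outcome model** (Primary analyses of efficacy): "Sick leave/insurance status will be calculated as risks of shifting between different states of sick leave, disability pension, and recovered". The separate states of sick leave are not listed and no starting state is fixed. A Cox model is mentioned only as a possibility.
- **Partial leave** (same section): "Partial recovery represented by partial sick leave will be accounted for".
- **Binary comparison** (same section): "The proportions of participants with a positive primary outcome will also be compared across the treatment groups", followed by a number needed to treat if there are differences. What makes an outcome positive is not defined.
- **Covariates** (same section): "Explanatory variables (treatment) and confounders (e.g. age, gender) will be included as in any regression model". The list is open, but the sick-leave level at entry is not named.
- **Who can enter**: the inclusion criteria require "At least 50% sickness compensation"; invitations go to "patients that have been at least 50% sick listed, for 2 to 10 months due to LBP"; the exclusion criteria remove only those "Less than 50% sick listed or not on sick leave anymore".
- **Stratification** (Randomization): "The list is stratified by clinic and gender". Entry level is not a factor.

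**The concern.** The marker is an absolute state, whereas recovery is a change. The two agree only if everyone starts on full sick leave, and the eligibility rules do not require that. A patient who enters at 50% and is still at 50% a year later has not recovered in any degree, yet sits in the state the plan treats as partial recovery.

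Sick leave is the main outcome, so the definition reaches the primary comparison. If partial leave were counted as success in the proportions, unchanged patients would be credited in every arm, and the number needed to treat would be computed on that mixture. In the transition analysis, entry into the partial state would mean different things for different patients unless the model takes account of where each one began.

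**Working it through.** **1. The plan's own figure.** Sample size calculations compares 40% off sick leave at 9 months with 60%, at 80% power and a 5% level. Sidedness is not stated; two-sided is assumed. With pooled variance and no continuity correction:

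n = [1.960 × √(2 × 0.5 × 0.5) + 0.842 × √(0.4 × 0.6 + 0.6 × 0.4)]² / 0.20²

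= (1.386 + 0.583)² / 0.04 = 96.9, so 97 per arm and 4 × 97 = 388.

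This matches the stated 97 and N = 388. The inputs are rates of being off sick leave. Partial leave does not enter, so the figure does not depend on how partial recovery is defined.

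**2. Does entry overlap with the marker?** Eligible levels run from 50% to 100%. Partial sick leave is any level above zero and below 100%. The overlap is every level from 50% up to, but not including, 100%. A patient there meets the inclusion criteria, avoids the exclusion criteria and is on partial leave at randomisation.

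**3. What the marker says, case by case.**

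- *Enters at 100%, later at 50%.* Absolute marker: partial recovery. Against own entry level: improved. The two agree.
- *Enters at 50%, still at 50%.* Absolute marker: partial recovery. Against own entry level: unchanged. They disagree.
- *Enters at 50%, rises to 100%, returns to 50%.* A transition model records a worsening and then an improvement, which is what happened. The end state is nevertheless the starting point, so labelling it partial recovery relative to entry is wrong.
- *Enters on partial leave above 50%, falls but stays on some leave.* If there is only one partial state, no transition is recorded although the patient improved.
- *Enters at any level, ends fully off sick leave.* Recovered under either definition.

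For patients who enter on full leave the two definitions always coincide, because any fall below 100% short of zero is partial leave. They differ only for patients who enter on partial leave.

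**4. Does anything in the article repair this?** No section defines recovery relative to entry, fixes the starting state, names entry level as a covariate or stratifies by it.

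**5. Size.** The number misclassified depends on the share entering on partial leave and on how many of them stay there. The article gives neither.

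**The case against.** The strongest reply is that nothing in the article scores partial leave as success. To account for partial recovery is not to count it as a positive outcome. The list of states keeps recovered apart from the states of sick leave, and the only binary endpoint with figures is being off sick leave. The first-named analysis concerns shifts between states, so an unchanged patient contributes no event, and conditioning on the state being left is how such models normally work. The remaining detail might belong in an analysis plan.

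Most of this stands, and it limits the point. It does not remove it: the article itself states the marker, and that marker does not fit the article's own entry rule for part of the eligible population. A model that conditions on the starting state is possible under the text but not promised.

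A reader might go further and infer a loss of power. If a share f entered on partial leave and were all counted as successes, with 40% and 60% for everyone else, the rates would be 0.40 + 0.60f and 0.60 + 0.40f. For f of 10% to 40% the 20-point difference would shrink to between 18 and 12 points, and power at 97 per arm would fall to between 71.5% and 44.5%. The documents do not support this inference:

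- It uses an endpoint the plan does not adopt.
- f has no source in the article.
- It assumes that no non-returning partial entrant ever moves to full leave or disability pension.
- It counts partial leave as success for partial entrants but ignores full-leave entrants who move to partial leave.

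It is also fair that absolute work status and change from entry are different estimands. Either can be chosen, but the word recovery fits only the second.

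**Conclusion.** The point holds as a defect of definition. The stated marker of partial recovery overlaps with the entry criteria, so it mislabels any patient who enters on partial leave and stays there. The share affected is unknown.

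The transition analysis is largely safe if patients start in their entry state. The proportions and the number needed to treat are safe if success means fully off sick leave. The article commits to neither. The sample size of 97 per arm stands, and no power loss can be claimed.

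A reader might also infer that the arms would be compared unfairly. That does not follow: randomisation balances entry level on average, so the expected harm is misclassification in all arms. Loss of precision from leaving entry level out of the models rests on the assumption, likely but not shown in the article, that entry level is prognostic.

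**What to change.** Amend the section on primary analyses of efficacy, before allocation is revealed, in four respects:

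1. Count partial recovery only when the sick-listed percentage falls below the patient's own percentage at randomisation.
2. Start each patient in the transition model in the entry state, partial or full.
3. Include the entry percentage as a covariate in the Cox, transition and proportion analyses.
4. State that a positive outcome in the proportions and the number needed to treat means fully off sick leave, matching the basis of the sample size calculation.

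The cost is slightly more analysis work. No new data collection is needed: the entry percentage must already be known to check eligibility, and sick-leave data come from the national insurance register. The sample size does not change. Fixing the definition while allocation is still concealed also prevents it from being chosen in the light of the results.

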#### Secondary analyses of efficacy

Any significant effects of any of the interventions will be estimated by a standard cost benefit formula [88-90], as used by Hagen et al [59]. Benefits will be measured in terms of increases in the net present social value of production, when intervention causes a reduction in the number of days on sick leave. This is calculated as the product of the treatment effect, i.e. the reduction in sick leave days, and the productivity gains for the society when a person works instead of receiving benefits. For each person the social value of production is based on mean earnings at inclusion in the treatment group. Cost of treatment also includes follow-up at the clinics. Potential differences in treatment costs between the groups, which are related to treatments received independent of the study, will be accounted for by follow-up questionnaires from the participants.

We will also evaluate health complaints/pain and disability as recorded by the questionnaires at 3, 6 and 12 months. Appropriate regression models, based on the distribution for the different outcomes, will be performed, including variables found to be statistically significant predictions.

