#### Secondary objectives

The secondary analyses are exploratory, but will be guided by previous findings.

1) What are the relative cost-effectiveness and cost-benefit of these interventions?

2) What is the prevalence of psychiatric disorders in this population of chronic LBP patients?

3) What baseline factors predict different treatment outcomes in the different intervention groups?

4) Will any of the interventions impact the cortisol profiles of the LBP patients?

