### Analyses

#### Sample size calculations

The sample size calculations were based on data from Hagen et al. [30] and the transition probabilities calculated for the intervention group in that study. The sample size was based on the transition probabilities at 9 months, where approximately 40% of the individuals had returned to work. Hagen et al. [59] found that the effects were largest for the earlier period after the intervention. This is therefore an argument to use 40% off sick leave at 9 months as the most relevant measure for effect in this study. This was compared to a hypothesized 60% return to work (RR 1.5) as an adequate effect size. The sample size calculations were based on standard formulas for calculating sample size, for studies comparing binomial proportions using the statistical package "R" (Library Hmisc). This may increase the power of the estimates in the analyses, since the simpler method used for the calculation does not include in this issue. All calculations were based on a power of 80% and a significance level of 5%.

Separate sample size calculations for males and females were computed. The total number of individuals should be approximately N = 4*n, where n is the calculated sample size and 4 is the number of arms in the study. The total number of males should be N = 4*65 = 260 and the total number of females N = 4*81 = 324. If we control for gender in the analysis instead of performing stratified analyses, we do not need to calculate separate sample sizes for men and women. The total number of participants should be 97 in each arm (N = 388). These numbers require a multi-centre design.

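### The cost-benefit formula is applied only to significant effects, although the economic objective is unconditional; non-significant comparisons get no estimate and those that pass are too large on average

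*Protocol article*

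**What the plan says.** Secondary objective 1 asks: "What are the relative cost-effectiveness and cost-benefit of these interventions". No condition is attached. The section introduces its objectives with "The secondary analyses are exploratory, but will be guided by previous findings".

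The only economic method described is under Secondary analyses of efficacy: "Any significant effects of any of the interventions will be estimated by a standard cost benefit formula". Benefit is then defined: "This is calculated as the product of the treatment effect, i.e. the reduction in sick leave days, and the productivity gains for the society". On valuation: "For each person the social value of production is based on mean earnings at inclusion in the treatment group". On costs: "Cost of treatment also includes follow-up at the clinics". The cost sentences carry no significance condition.

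Two other places matter. Under Hypotheses of efficacy, seal oil is expected to reduce health complaints but to have no influence on return to work or sick leave. Under Primary objectives, CBT is compared with BI alone, seal oil with BI alone or placebo, and CBT with seal oil.

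**The concern.** A question about relative cost-benefit needs an estimate for each comparison. Filtering on significance has two consequences.

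- **Missing results.** A comparison that misses significance has no cost-benefit estimate. Yet an intervention that adds cost for an uncertain gain is where those who pay for care most need net benefit with its uncertainty. Benefit is defined only through sick-leave days, and seal oil is hypothesised not to change these. On the article's own hypothesis, that arm would normally have no result.
- **Selected results.** Estimates that clear a significance threshold exceed the truth on average. The formula multiplies the selected effect by a money value, so the excess carries straight into the benefit. Costs are not selected in the same way, so net benefit is pushed upward.

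**Working it through.** **Inputs from the article (Sample size calculations).** Control rate: "The sample size was based on the transition probabilities at 9 months, where approximately 40% of the individuals had returned to work". Target: "This was compared to a hypothesized 60% return to work (RR 1.5) as an adequate effect size". Power is 80%, the significance level is 5%, and there are 97 per arm (N = 388).

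**Step 1: reproduce the sample size.** The calculation is two-sided, with no continuity correction and mean proportion 0.5:

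n = [1.96·√(2·0.5·0.5) + 0.8416·√(0.4·0.6 + 0.6·0.4)]² / 0.20² = (1.386 + 0.583)² / 0.04 = 96.9, so 97 per arm, and 4·97 = 388. This matches the article exactly.

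**Step 2: where the filter bites.** With 39/97 in the control arm, the smallest significant favourable result is 53/97, a difference of 14/97 = 14.4 points. The pooled proportion is 92/194 = 0.474, the SE is √(0.474·0.526·2/97) = 0.0717, and z = 0.1443/0.0717 = 2.01. With 52/97, z is 1.87. At that control rate, a smaller observed gain would never be valued.

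**Step 3: effect of the filter.** Two million two-arm trials were simulated for each scenario (97 per arm, control rate 40%, pooled z-test at two-sided 5%). True gains below 20 points are assumptions.

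| True gain (points) | No significant result | Mean estimate when significant and favourable | Ratio to truth |
|---|---|---|---|
| 20 (design) | 19% | 22.4 | 1.12 |
| 15 | 44% | 20.0 | 1.33 |
| 10 | 71% | 18.4 | 1.84 |
| 0 | 95% | – | – |

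The normal-approximation power at the design effect is 80.0%, so the 19% could equally be given as 20%. The last row corresponds to the article's hypothesis for seal oil on return to work. Without the filter, no comparison lacks a result and there is no selection bias.

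**Step 4: from effect to money.** Let B be the true benefit (effect times value), C the cost and k the ratio in the table. The average reported net benefit is kB − C instead of B − C, an excess of (k − 1)·B. At the design effect this is 0.12·B.

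**Step 5: the earnings base.** The article gives no spread of earnings, so a coefficient of variation (CV) of 0.2 to 0.5 is assumed. The SE of one arm's mean is CV/√97 = 2.0% to 5.1%. The SE of the difference between two arms is CV·√(2/97) = 2.9% to 7.2%. Take an assumed true effect of 20 days (200 v 180 sick days of 365), with earnings drawn independently of the effect:

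- *One effect times the treated arm's wage:* the mean is 20.0 wage-days, with SD 0.6 (CV 0.3) to 1.0 (CV 0.5). An imbalance of +5% gives 20·1.05 = 21.0; −5% gives 19.0.
- *Each arm's working days at its own wage:* the mean is 20.0, with SD 7.6 to 12.6. An imbalance of +5% gives 185·1.05 − 165 = 29.25; −5% gives 185·0.95 − 165 = 10.75.

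Both readings are centred on 20. They add noise and no systematic overstatement.

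**The case against.** **The figures are not from the planned analysis.** Benefit is measured in sick-leave days, and the primary analysis uses transition models, possibly Cox. The article suggests these may have more power than the binomial calculation. This stands: the table is a proxy, and its lower rows rest on assumed effects. A reader might take 71% and 1.84 times as the expected performance of this trial. The documents do not support that, since their own planning value gives 19% and 1.12 times. The direction of the selection effect does not depend on which test is used.

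**Only cost-benefit is filtered.** A reader might infer that the whole economic objective goes unanswered. The text does not say so: it sets no significance condition on cost-effectiveness or on the cost sentences. The conflict concerns the cost-benefit half of the objective.

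**The earnings rule is not a bias.** A reader might infer that each arm is valued at its own mean earnings and that benefit is overstated as a result. The article describes one effect multiplied by one productivity value, so a zero effect gives zero benefit. Which group is meant is unclear, and own-arm valuation is only one possible reading. Earnings are taken at inclusion in randomised arms, so any imbalance is due to chance and can go either way. Under the product formula it is also small: the SE of the effect itself is √(0.48/97) = 7.0 points, or 35% of a 20-point effect.

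**The analysis is exploratory and the article is condensed.** This limits the weight of the point. It does not justify the condition, because exploratory work calls for estimates with intervals. The condition is also printed in the article, so the point does not rest on an omission.

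**Conclusion.** The significance condition contradicts the unconditional objective and should be removed. As printed, it withholds a cost-benefit estimate from every non-significant comparison and inflates those that are reported. On the binary proxy at the design effect, about one comparison in five has no result and the reported effects run 12% high on average. Both problems grow as the true effect shrinks. These sizes assume a two-sided 5% test of 40% v 60% (or the smaller gains shown) with 97 per arm.

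The overstatement comes from the significance condition alone. The earnings phrase needs clarifying, but nothing in the article shows that it biases the benefit. The weight is moderate, because the analysis is secondary and exploratory.

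**What to change.** Delete the significance condition and state, for example: *Costs, benefit (difference in sick-leave days times productivity value) and net benefit will be estimated with 95% confidence intervals, whatever the p-value, for every comparison in the protocol. These include BI and CBT v BI only, BI and seal oil v BI and soy oil (placebo), and BI and CBT v BI and seal oil.*

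The last comparison must be kept, because the second primary objective asks for it.

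As a clarification only, name one common baseline earnings value, for example the mean at inclusion pooled over all randomised patients. This removes chance noise between arms and settles the ambiguity; it does not correct a systematic bias.

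The cost is a little more analysis. The register data on sick leave and the questionnaire data on outside treatment are already planned.
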